**Primary analysis**

The primary evaluation end point will be the fasting glycaemia before and after supplementation. It will be compared within groups and between the two groups using a test of comparison of means.

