| Primary endpoint | Fasting glycaemia in prediabetic overweight subjects before and after nutritional intervention |
| Secondary endpoints | To study the influence of 4-month supplementation with Glycabiane on lipid profile (Total cholesterol, LDL-c, HDL-c, TG, etc.), levels of glycosylated haemoglobin, anthropometric characteristics and on the biology of adipose tissue (size of adipocytes, inflammatory status, sensitivity to insulin.  To evaluate safety of 4-month supplementation with Glycabiane  To evaluate quality of life |
| Methodology/Study design | A single centre, randomised, double-blind, placebo-controlled study |
| Criteria for inclusion of subjects | Men and women 25-65 years of age:  - prediabetic: 1.00 g/L ≤ fasting glycaemia < 1.26 g/L,  - overweight or obesity (BMI>25),  - with normal renal and hepatic function tests,  - covered by the French social security system,  - sufficiently cooperative to comply with requirements of the study,  - patients with immunocompetent status (no known HIV or hepatitis C infection),  - use of an effective method of contraception by women of childbearing potential. |
| Criteria for Non-Inclusion of Subjects | - thyroid disorder - hypogonadism - history of a musculo-skeletal, auto-immune or neurological disorder - Hepatitis C, HIV - Medical therapy for thyroid disease, hypoglycaemia or use anti-coagulant therapy - pregnant women or breastfeeding mothers - subject under measure of legal protection - subject who received fees of €4,500 as compensation for participation in clinical trials during the last 12 months. This information is to be verified by the investigator, since subjects are compensated in the study - history of allergy to one of the components of the investigational product - contra-indication to use of xylocaine as a local anaesthetic |
| Number of Patients | 50 subjects: 25 subjects per group |
| Duration of Study | Duration of the inclusion period: 6 months  Duration of participation for each patient: 6 months  Total duration of study: 24 months |
| Expected findings | This first randomised, double-blind, placebo-controlled study of a new combination cinnamon/chromium represents important hope in order to regulate fasting glycaemia in prediabetic overweight subjects with a nutritional product and with a physiological dose in order to limit progression of prediabetes to type 2 diabetes. |

TABLE OF CONTENTS

[I. Study rationale 7](#__RefHeading___Toc394046426)

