### Description of participating persons:

Criteria for inclusion

- Men and women 25 to 65 years of age,

- Who satisfy the following criteria:

- 1.0 g/L ≤ fasting glycaemia < 1.26 g/L

- Overweight or obese (BMI ≥ 25)

- Who do not wish to change their dietary habits and physical activity,

- With normal renal and liver function test evaluations,

- Covered by the French social security system,

- Sufficiently cooperative to comply with requirements of the study,

- Immunocompetent status (no known HIV nor hepatitis C virus),

- Use of an effective method of contraception for women of childbearing potential

Criteria for exclusion

- thyroid disease
- hypogonadism

- history of a musculo-skeletal, auto-immune or neurological disorder

- hepatitis C, HIV

- medical therapy for thyroid disease, hypoglycaemia or anti-coagulant therapy

- medical therapy than can have an influence on:

- weight gain/loss

- glycaemic control

- serum insulin

- pregnant women or nursing mother

- weight loss > 5% during last 6 months

- ingestion of a dietary supplement containing cinnamon or chromium

- subject who is under legal protection,
- subject who collected €4,500 as compensation for participating in clinical trials during the last 12 months. This information is to be verified by the investigator, subjects are compensated in research studies
- history of allergy to one of the components of the investigational product
- contra-indication to use of xylocaine as a local anaesthetic

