### Number of persons to include:

Calculation of sample size: 25 subjects per group are necessary to demonstrate a change in fasting glycaemia of at least 10% and of a standard deviation 0.13 g/L (mean of standard deviations observed in clinical studies published on type 2 diabetes and cinnamon), setting an risk of 0.05 and a  risk of 0.10. 60 subjects will be selected in the study according to criteria for inclusion and non-inclusion to ensure inclusion and follow-up of the study for 50 subjects in its totality.

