# Statistical analysis of data

## Number of subjects necessary

Based on the literature, a 10% decrease in fasting glycaemia can be expected in the Glycabiane group compared to the Control group, after 4 months of supplementation. The statistical hypothesis is a 10% difference in the primary evaluation end point (Fasting glycaemia) between subjects who received the placebo and those who received Glycabiane®. Therefore, the number of subjects to be enrolled in this trial, with an alpha risk of 5% and a power of 90%, is 25 per group, i.e. a total of 50 subjects. 60 subjects will be screened in the study to ensure inclusion and follow-up of a total of 50 patients.

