**Secondary analyses**

Other comparisons (secondary evaluation end points) will be:

- levels of HbA1c before and after supplementation. Comparison will be performed within groups and between the two groups.

- concentrations of total cholesterol, HDL-c, LDL-c, TG, ND leptin before and after supplementation. Comparison will be performed within groups and between the two groups

- serum insulin and HOMA before and after supplementation, within groups and between the two groups comparison

- quality of life before and after supplementation

- systemic inflammatory status (IL-6, CRPus)

- adipocyte size before and after supplementation

- inflammatory status of adipose tissue in vitro by ELISA assay measurement (IL-6, adiponectin)

- sensitivity to insulin of adipose tissue in vitro by study of adiponectin secretion and of Akt phosphorylation

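### The primary analysis sets before/after tests within each group beside the between-group test without saying which decides, and no named method adjusts for the D0 value

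*Protocol*

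**What the plan says.** - **Primary endpoint.** The Synopsis gives it as "Fasting glycaemia in prediabetic overweight subjects before and after nutritional intervention". The Primary analysis section repeats this: "The primary evaluation end point will be the fasting glycaemia before and after supplementation". Neither says whether the month-4 value or the change is compared.
- **Primary test.** "It will be compared within groups and between the two groups using a test of comparison of means". No order is set among the three comparisons and no covariate is named.
- **Hypothesis.** Under Number of subjects necessary: "The statistical hypothesis is a 10% difference in the primary evaluation end point (Fasting glycaemia) between subjects who received the placebo and those who received" the active product. The error rates and sample size belong to that comparison: "with an alpha risk of 5% and a power of 90%, is 25 per group, i.e. a total of 50 subjects".
- **General method.** Under Statistical considerations, quantitative data are to be analysed by repeated-measures ANOVA or MANOVA, with tests at 5%. Nothing links this to the simple test of means in the Primary analysis section.
- **Secondary endpoints.** For HbA1c, and in near-identical words for lipids, leptin, insulin and HOMA: "Comparison will be performed within groups and between the two groups".
- **Baseline data.** The flowchart has fasting glycaemia measured at V1 (screening), V2 (D0), V4 (month 4) and V5 (month 6).

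**The concern.** The trial has a placebo arm so that whatever would have happened without the product can be subtracted. A before/after test in the active arm does not subtract it. If both arms fall for a shared reason, such as selection on a raised value or the effect of being in a trial, that test can be significant for an inert product.

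As written, a report could present a significant fall on the product and a non-significant one on placebo under the heading of the primary analysis, with no difference shown between the arms. The misreading is a realistic one. The Protocol's own summary of the cited placebo-controlled prediabetes study gives the before/after fall in the cinnamon arm and no placebo change.

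There is a second, smaller issue. Every subject has a D0 value, and two analysis methods are named, but neither conditions on that value. Which method the 90% power refers to is not stated.

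**Working it through.** **1. The planned sample size.** Inputs: a 10% difference, SD 0.13 g/L, alpha 5%, power 90%. The value to which the 10% applies is not stated, so it is assumed from the entry range, "1.0 g/L ≤ fasting glycaemia < 1.26 g/L", or from the cited prediabetes baseline of 1.163 g/L.

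n per group = 2 × (0.13/δ)² × (1.960 + 1.282)², two-sided

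| Base (g/L) | δ (g/L) | n per group |
|---|---|---|
| 1.00 | 0.100 | 36 |
| 1.13 (midpoint of entry range) | 0.113 | 28 |
| 1.163 | 0.1163 | 27 |
| 1.20 | 0.120 | 25 |
| 1.26 | 0.126 | 23 |

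The planned 25 is reproduced by an unadjusted two-group comparison with a base of about 1.20 g/L. The powered test is therefore the between-group one.

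**2. The within-group test when the product does nothing.** The placebo arm of the cited 4-month trial (table under Nutritional intervention) changed by -3.37 ± 14.2%; the 14.2% is taken as an SD. Let both arms of this trial behave that way, with n = 25 in each.

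- Noncentrality of the paired t test: 3.37 / (14.2/√25) = 1.19, on 24 degrees of freedom.
- P(significant fall in one arm) = 0.206. With no shared fall it would be 0.025.
- P(active shows a significant fall, placebo not significant) = 0.206 × (1 − 0.207) = 0.163.

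The same calculation in g/L uses a shared fall of 0.038 g/L (3.37% of 1.13) and assumed SDs of change:

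| SD of change (g/L) | Significant fall in active arm | Active significant, placebo not |
|---|---|---|
| 0.154 | 22% | 17% |
| 0.130 | 29% | 21% |
| 0.100 | 45% | 25% |

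In a simulation of 200,000 trials per setting (SDs of change 0.154, 0.130 and 0.101), the between-group test rejected in 5% throughout.

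**3. What baseline adjustment could add.** The inputs are δ = 0.113 g/L, 25 per group, two-sided 5%, two-sample t power. Two assumptions are needed: that 0.13 g/L is the SD of a single value, and the correlation ρ between the D0 and month-4 values.

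- Month-4 value, unadjusted: SD 0.13, power 85%.
- ANCOVA: SD = 0.13 × √(1 − ρ²).
- Change score: SD = 0.13 × √(2(1 − ρ)). With two visits, the group-by-time test of a repeated-measures ANOVA is this test.

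| ρ | ANCOVA SD | ANCOVA power | Change-score SD | Change-score power |
|---|---|---|---|---|
| 0.3 | 0.124 | 88% | 0.154 | 72% |
| 0.5 | 0.113 | 94% | 0.130 | 85% |
| 0.6 | 0.104 | 96% | 0.116 | 92% |

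The two methods the Protocol names can thus differ in power by 13 points at ρ = 0.3 (85% against 72%). They are equal at ρ = 0.5.

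**The case against.** **The hypothesis is already between groups.** The sample-size section attaches the hypothesis, alpha and power to the difference between product and placebo. A reader might infer from the Primary analysis section that a before/after result is the declared basis of success. The documents do not support that: such a result would not answer the stated hypothesis. What stands is that the section describing the test does not carry that hypothesis through as a decision rule.

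**Baseline is not ignored.** Repeated-measures ANOVA uses the D0 value, as a response. This is correct, so it would be wrong to say that baseline plays no part. What stands is that the two methods are not reconciled and neither adjusts for D0 as a covariate.

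**An unadjusted randomised comparison is valid, and covariates are often left to the SAP.** Also correct. A reader might infer that substantial power is being thrown away, but the Protocol gives no correlation. Entry restricted to a narrow glycaemia range makes a low one plausible, and at 0.3 the gain is 3 points. The Protocol is also unclear on what its SD describes: "demonstrate a change in fasting glycaemia of at least 10% and of a standard deviation 0.13 g/L". If 0.13 g/L is the SD of the change, the table in step 3 does not apply.

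**The error rates rest on borrowed figures.** The placebo fall comes from poorly controlled type 2 diabetes, not prediabetes. Much of any regression from the V1 selection value may also have occurred before D0. Both points make the rates illustrative. A reader might also count trials with at least one significant within-group test, about 37% on the cited trial's figures. That includes trials significant on placebo only, which nobody would report as efficacy.

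**Conclusion.** The point holds in a limited form. The primary analysis mixes within-group and between-group tests with no rule for which decides, and it is not aligned with the between-group hypothesis or with the repeated-measures method given elsewhere in the Protocol.

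On the cited trial's own placebo figures, an inert product gives a significant within-group fall in about 21% of trials. The pattern of active significant and placebo not occurs in about 16%, or 17 to 25% for a shared fall of 0.038 g/L with an SD of change of 0.154 to 0.10 g/L. These rates assume 25 per group, the same fall in both arms, and that figures from type 2 diabetes carry over. The between-group test is unaffected, so the risk comes only from giving the within-group tests primary standing.

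The case for ANCOVA is a recommendation: it costs nothing and is at least as efficient as either alternative, apart from one degree of freedom. Its gain cannot be sized from the Protocol.

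**What to change.** - **Primary analysis:** make the sole primary test the between-group difference in month-4 (V4) fasting glycaemia, by ANCOVA with group and the D0 (V2) value as terms, two-sided at 5%, with the estimate in g/L and its 95% confidence interval.
- **Within-group changes:** report them descriptively, without p-values.
- **Statistical considerations:** align the repeated-measures sentence, for example by limiting it to supportive description over visits, so that one method governs the primary endpoint.
- **Secondary analyses:** use the same between-group model for the quantitative endpoints measured at both D0 and V4.

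The cost is a few sentences of wording, to be settled before unblinding. All the data needed are already scheduled, and the sample size need not change for this reason.

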**Secondary analyses**

Other comparisons (secondary evaluation end points) will be:

- levels of HbA1c before and after supplementation. Comparison will be performed within groups and between the two groups.

- concentrations of total cholesterol, HDL-c, LDL-c, TG, ND leptin before and after supplementation. Comparison will be performed within groups and between the two groups

- serum insulin and HOMA before and after supplementation, within groups and between the two groups comparison

- quality of life before and after supplementation

- systemic inflammatory status (IL-6, CRPus)

- adipocyte size before and after supplementation

- inflammatory status of adipose tissue in vitro by ELISA assay measurement (IL-6, adiponectin)

- sensitivity to insulin of adipose tissue in vitro by study of adiponectin secretion and of Akt phosphorylation

# Cnil[[5]](#footnote-6)

This study falls within the scope of the “Methodology of Reference” (MR-001) in application of conditions of law of 6 August 2004 relating to protection of physical persons regarding processing of personal data and modifying law of 6 January 1978 relating to data processing, computer files and freedoms. This change has been certified by decision of 5 January 2006.

# Archiving

PiLeJe, in its capacity as the sponsor, saves documents and data relating to the trial in compliance with legislative and regulatory conditions in force, in particular, the decision of 8 November 2006 setting the duration of storage by the sponsor and the investigator of documents and data relating to a biomedical research study involving a medicinal product for human use.

This duration of storage of documents is set at 15 years.

Documents concerned are the following, in particular:

- the investigator brochure;
- the study protocol and any possible amendments signed, specimens of case report forms and operating diaries and all documents/media used to collect data;
- information communicated to the person who is the subject in the study and forms for collection of his or her consent;
- financial aspects of the study;
- insurance policy covering the sponsor’s civil responsibility and an insurance certificate delivered by the insurance company;
- contracts or agreements signed between the different persons (sponsor, CRO, investigators, etc.);
- dossier requesting an opinion from the CPP, exchanges of correspondence and opinions from the CPP;
- names of persons in the CPP who took part in the deliberations on the research project;
- *Curriculum vitae* of investigators and of collaborators involved in the study, list of the investigators’ assistants ;
- Completed case report forms, dated and signed;
- AE, SAE, USAE forms.

PiLeJe, in its capacity as the sponsor, informs the investigators in writing of the need to save documents and data relating to the study up until it is notified to them that such documents no longer are necessary.

# Communication

Data will be disclosed only after the prior joint agreement of the investigator and of the sponsor. Results will be the subject of communications and published articles.

Furthermore, at the end of the study, persons who were subjects in the study have the right to be informed of overall results of the study, according to modalities which will be specified in the information document (article L. 1121-1 of the Public Health Code).

# Substantial changes to the protocol

Changes made to the protocol must be qualified as substantial or not.

Depending on their type, they will be subject to another opinion from the Committee for the Protection of Persons and AFSSAPS.

Any substantial change to the protocol concerning the study objectives, its design, population, tests or significant administrative aspects will require approval by the investigator, the sponsor, and a favourable opinion of the CPP. Another consent form for persons participating in this study will be collected, if necessary.

# Confidentiality

## Access to data

The sponsor is in charge of obtaining consent from all parties involved in the study in order to ensure direct access to all of the places where the study is conducted, to source data and reports for the purpose of quality control and an audit by the sponsor.

Investigators will make available individual documents and data strictly necessary for follow-up, quality control and an audit of the biomedical research study will be made available to persons with access to documents in compliance with legislative and regulatory conditions in force (articles L.1121-3 and R.5121-13 of the Public Health Code).

## Source data

Since source documents are defined as any original document or object making it possible to prove the existence or accuracy of data or a fact recorded during the clinical study will be kept during 15 years by the investigator or by the hospital if it involves a hospital medical dossier. In this study, only the medical dossier is considered as source data.

## Confidentiality of data

In compliance with conditions concerning confidentiality of data to which persons in charge of quality control of a biomedical research study have access (article L.1121-3 of the Public Health Code), in compliance with conditions relating to confidentiality of information, in particular, concerning the nature of the investigational products, tests, persons who are subjects in this study and results obtained (article R. 5121-13 of the Public Health Code), persons with direct access will take all necessary precautions to ensure the confidentiality of information relating to investigational medicinal products, tests, persons who are subjects and, in particular, concerning their identity, as well as the results obtained.

These persons, in the same capacity as the investigators, are subject to professional secrecy (according to conditions defined by articles 226-13 and 226-14 of the Penal Code).

During the biomedical research study or at its end, data collected on persons who are subjects and sent to the sponsor by the investigators (or all other specialised participants) will be made anonymous.

The names of persons concerned, nor their address, in any case must not be clearly legible.

Only the first three letters of a subject’s surname and the first two letters of their first name will be recorded, together with a code number specific for the study indicating the order of inclusion of subjects.

The sponsor will ensure that each person who is a subject in the study has given his or her agreement in writing for access to individual, personal data strictly necessary for quality control of the study.

## Registration in the national file of persons who are subjects in biomedical research

In application of article L. 1121-16 of the public health code, the names of persons who are subjects in biomedical research will be recorded in a national file of persons who are subjects in biomedical research: VRB (Volunteer Subjects for Biomedical Research)

The investigators will be the only persons authorised to enter the names of volunteers in this file.

# Quality assurance

## Commitment by investigators and sponsor

The investigator agrees that this study will be conducted in compliance with public health law no. 2004-806 of 9 August 2004 concerning biomedical research, application decision no. 2006-477 of 26/04/2006 modifying chapter Ititle II of book 1 of the 1st part of the Public Health Code relating biomedical research, as well as the decisions in force.

Rules on good clinical practice (GCP) for biomedical research on medicinal products for human use, mentioned in article L. 1121-3 of the Public Health Code and decision of 24 November 2006 will also be applied (see Appendix 10).

The investigator also agrees to work in agreement with the Declaration of Helsinki of the World Medical Association (Tokyo 2004, revised version). (See Appendix 9).

## Quality Assurance

A Clinical Research Associate (CRA) mandated by the sponsor will ensure proper conduct of the study, the collection of data generated in writing, their documentation, recording and report, in agreement with Procedures and in compliance with Good Clinical Practice, as well as legislative and regulatory conditions in force.

## Quality control

The investigator is the guarantor of the authenticity of data collected in the setting of the study and accepts legal conditions authorising the sponsor of the study to set up quality control.

The investigator and co-investigators therefore accept to make themselves available at visits for Quality Control performed at regular intervals by the Clinical Research Associate. At these visits, the following items will be reviewed:

- informed consent and information forms;
- compliance with study protocol and procedures defined in them;
- quality of data collected in the case report forms: accuracy, missing data, consistency of data with “source” documents (medical dossiers, log books of appointments, originals of laboratory test results, etc.);
- management of products.

